# Trial objectives and Design

### 3.1 Trial objectives

The overall aim of this project is 1) to evaluate the effectiveness of a nurse-led geriatric-traumato co-management program using outcome indicators and 2) to evaluate the implementation of a nurse led geriatric-traumato co-management program

### 3.2 Primary endpoints

1) Effectiveness evaluation

- In-hospital complications, including and limited to:

1/ Delirium: on suspicion of delirium the 4AT^9^ will be used to make the diagnosis. Mini-Cog^9^ will be used to assess the cognitive status of the patient

2/ Congestive heart failure: note in the electronic patient record of heart failure

3/ Pneumonia: diagnosis based on imaging or laboratory testing

4/ Deep venous thrombosis or pulmonary embolism: confirmed on imaging

5/ Myocardial infarction: diagnosis stated in the electronic patient record based on clinical image and laboratory testing/ECG findings.

6/ Urinary tract infection based on laboratory testing and needing treatment with antibiotics

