- the fidelity towards the core components of the program (% of included patients who received the core components of the intervention). The core components are 1) the screening questionnaire, 2) comprehensive geriatric evaluation, 3) individual care plan and 4) follow-up.

- The fidelity towards the other intervention components:

- Patient received physiotherapy within 24h postoperative
- The patient was evaluated using the food quadrant method by a logistics employee
- Patient received swallowing screening by a nurse
- If there is no indication for an indwelling catheter, the patient is free of an indwelling catheter
- If a post-void residual volume of ≥ 300 ml is observed in a patient, the residual volume is removed using intermittent catheterization before end of shift after detection of symptoms
- If the urinary catheter was removed, the post-void residual volume is monitored using a bladder scan in the next shift
- If a patient has not passed stool for 3 days, the patient is prescribed oral laxatives before day 4 without stool
- If a patient has not passed stool for 5 days, the patient receives an enema before day 6 without stool
- If there is no indication for a physical restraint, the patients is free of a physical restraint
- If a patient is delirious, the DOS scale was followed up during the next shift
- If a patient reports a pain score of 4 or higher (out of 10), pain medication is given unless refused by the patient within 1h of onset of symptoms
- If a patient reports a pain score of 4 or higher (out of 10), the pain is re-evaluated within 1h of onset of symptoms
- If a patient did not take calcium/vitamin D supplements or anti-osteoporotic medication at admission, it was prescribed at discharge
- The patient was referred to a fracture liaison service

2.2: Implementation targets: awareness, knowledge, motivation to change, perceived acceptability and feasibility, and believe in the benefit, value and success of the program

2.3: Implementation determinants: facilitators and barriers of the program

3. Process evaluation (how well was the process of care changed?)

3.1: reach and fidelity will be reevaluated the same way as expressed above.

3.2: process outcomes

- time to start physiotherapy (as first day after surgery with a first registered contact in electronic patient record)

- % of patients receiving dietary advice and time to start dietary advice

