### 3.4 Trial Design

single-centre pre-post implementation study on the traumatology ward of the University Hospitals Leuven

**Usual care (pre-cohort):** the control group receives usual care on the traumato ward. This means that the patient is cared for by a surgical resident. The interprofessional team furthermore consists of ward nurses, a physiotherapist, an occupational therapist and a social worker. No tailored geriatric protocols are available to the traumato team, except for those that are available hospital-wide for all patients (e.g. fall prevention, delirium). Geriatric expertise is available upon active request by the traumato team and includes the comprehensive evaluation of the patient by a geriatric nurse (consultation model).

Due to the design of the G-COMAN strategic project and its predefined strict timing schedule (a phased implementation with the need of a rapidly full implementation), the timeframe for inclusion of the pre-cohort is limited. At the end of the pre-cohort, the predefined sample size will not be reached. To obtain sufficient included patients in the pre-cohort, this patient cohort will be supplemented with patients of which retrospectively information will be gathered. This results in a pre-cohort that will be partly prospective and partly retrospective.

**Geriatric co-management intervention, quality-improvement project G-COMAN (post-cohort):** A dedicated traumato nurse (G-COMAN nurse) will systematically perform a frailty screening in all newly admitted older patients on the traumato ward to evaluate if they are to be included in the G-COMAN program. In eligible patients, a comprehensive geriatric assessment (CGA) will be performed by the G-COMAN nurse. Based on identified potential problems, a tailored care plan based on predefined geriatric protocols will be launched. As part of the project a geriatric specialist nurse will provide every weekday training and education of the G-COMAN nurse and other team members on the traumato ward. The implementation of automated care plans and predefined geriatric protocols will be coordinated by a G-COMAN project coordinator, as well as the organisation of focus groups and intervisions to ensure smooth and supported collaboration.

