### At discharge

The research assistant will monitor the incidence of complications using patient assessment (4AT) and by monitoring the patients record throughout hospitalization, and will assess the outcomes on hospital discharge using patient interview. **Discharge date, medication and mortality** will be evaluated based on the electronic patient record. **Functional status** is measured using the Parker Mobility Score^11^, Barthel Index ^12^, Katz index and Lawton and Brody scale based on reports, if possible from the patient, from next of kin or from nursing staff. **Quality of life** will be evaluated using the EQ-5D questionnaire. **Fall history** will be evaluated using a questionnaire. **Cognition** will be assessed using the Mini-cog test. **Living situation** will be defined within the next 5 categories: living alone at their own home, living with a spouse/partner at their own home, living with children or sibling, living in assisted living facility, living in a facility with 24u care (nursing home, rehabilitation setting,…). Details of care provided will be recorded as one of the following categories: 24h care, daily, irregular, no care. Variables that can be retrospectively collected are as follows: discharge date, medication, mortality, fall history and living situation.

Also **several process outcomes** of the G-COMAN program will be evaluated using registrations in the electronic patient records and by patient interviews: reach of the program (% of eligible patients that were effectively enrolled into the program), fidelity to the program (% of patients included in G-COMAN traumatology program who had a screening or assessment focusing on *delirium, nutritional status, pressure ulcer risk* using a validated tool within 48h of admission to traumatology ward) and specific care process; such as the *time to start physiotherapy*; *time to start dietary advice*; use, *type and duration of fixation;* *use, duration and reason of indwelling catheters (urinary tract catheter or intravenous catheter); medication reconciliation; referral to geriatric day clinic* for follow-up; *and referral to a fracture liaison service (Zoledronate infusion or metabolic bone consultation).*

*Cost-benefit will be calculated by UHL financial division using the UHL cost model based on retrospective data collected at least 3 months post-discharge.*

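### The trigger for the 4AT differs between sections 3.2 and 5.1, and a suspicion rule may let the programme raise delirium detection in the post-cohort

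*Protocol*

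**What the plan says.** Protocol section 3.2 lists six groups of in-hospital complications as the primary endpoint. Delirium comes first, with the rule "on suspicion of delirium the 4AT" is used to make the diagnosis. Section 5.1 (At discharge) describes the data collection: "The research assistant will monitor the incidence of complications using patient assessment (4AT) and by monitoring the patients record throughout hospitalization". It gives no suspicion condition and no frequency. The flowchart in section 3.6 lists 4AT and record for the prospective cohorts and record only for the retrospective pre-cohort, which does not settle the question.

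Several programme elements exist only in the post-cohort. Under section 3.4 the G-COMAN nurse "will systematically perform a frailty screening in all newly admitted older patients on the traumato ward" and performs a comprehensive geriatric assessment in eligible patients, and "a geriatric specialist nurse will provide every weekday training and education of the G-COMAN nurse and other team members". Section 5.1 defines fidelity as the share of programme patients with a "screening or assessment focusing on *delirium, nutritional status, pressure ulcer risk* using a validated tool within 48h of admission to traumatology ward". Section 3.3 adds a fidelity item: "If a patient is delirious, the DOS scale was followed up during the next shift".

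In usual care, section 3.4 offers geriatric expertise on request only, but notes that hospital-wide protocols, with delirium as an example, are available to the team. The same section states that outcome assessors are not blinded.

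**The concern.** If the 4AT is given only when delirium is suspected, an unsuspected case, for instance a quiet hypoactive one, is not an event. The number of recorded cases then depends on how alert the ward is as well as on how often delirium occurs. The programme is designed to make the ward more alert. At the same true incidence, a more alert ward would record more delirium after implementation, which pushes the comparison towards no effect or apparent harm.

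This is separate from the difference between record-only and prospective data, because it would remain if only prospective patients were compared. Delirium also matters to the expected result: the Background section cites 13% less delirium in the sponsor's earlier cardiology programme.

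**Working it through.** **The plan's own figure.** Section 8.1 gives 108 per group for a 20-point absolute reduction, two-sided alpha 0.05, power 0.80 and 5% loss. With 71% v 51% and a continuity correction, n = 102, and 102/0.95 = 107.4, so 108. The sample size is not in dispute. Evaluable patients are 108 × 0.95 = 102.6, taken below as 102 or 103.

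**Inputs.** The protocol gives no delirium rate, no rate for the other complications and no detection share, so all of these are assumptions. Both scenarios use a true delirium reduction of 13 points, reading the Background figure as absolute, and treat delirium as independent of the other complications.

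- Scenario A: delirium 30% v 17%, other complications 40% v 28%, 103 per group.
- Scenario B: delirium 35% v 22%, other complications 38.5% v 23.1%, 102 per group. These were chosen to give 60% v 40% overall, the planned 20 points.

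**Formulas.** Recorded delirium = true rate × share detected. Any complication = 1 − (1 − recorded delirium)(1 − other). Power = Φ[(d − 1.96·SE0)/SE1], where SE0 = √(2p̄(1−p̄)/n) and SE1 = √([p0(1−p0) + p1(1−p1)]/n).

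**Example (A, 50% pre, 80% post).** Recorded delirium is 0.30 × 0.5 = 15.0% v 0.17 × 0.8 = 13.6%. Any complication is 1 − 0.850 × 0.60 = 49.0% v 1 − 0.864 × 0.72 = 37.8%, so d = 11.2 points. With p̄ = 0.434, SE0 = 0.0691 and SE1 = 0.0686, power = Φ(−0.34) = 0.37.

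| Scenario | Detection pre/post | Recorded delirium | Any-complication difference | Power | Difference if post detection equalled pre |
|---|---|---|---|---|---|
| A | 100%/100% | 30.0% v 17.0% | 17.8 | 0.73 | 17.8 |
| A | 70%/80% | 21.0% v 13.6% | 14.8 | 0.57 | 16.0 |
| A | 50%/80% | 15.0% v 13.6% | 11.2 | 0.37 | 14.9 |
| B | 100%/100% | 35.0% v 22.0% | 20.0 | 0.82 | 20.0 |
| B | 80%/90% | 28.0% v 19.8% | 17.4 | 0.70 | 19.1 |
| B | 60%/80% | 21.0% v 17.6% | 14.8 | 0.57 | 18.2 |
| B | 50%/90% | 17.5% v 19.8% | 10.9 | 0.35 | 17.7 |

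The last column applies the pre-cohort share to both groups. For A at 50%, for example, 1 − 0.850 × 0.60 = 49.0% and 1 − 0.915 × 0.72 = 34.1%, a difference of 14.9. It separates two effects. With the small gaps (A 70%/80%, B 80%/90%) the difference falls by 3.0 and 2.6 points, of which the imbalance itself accounts for 16.0 − 14.8 = 1.2 and 19.1 − 17.4 = 1.7. With the large gaps (A 50%/80%, B 50%/90%) it falls by 6.6 and 9.1 points, of which the imbalance accounts for 3.7 and 6.8. In the last row a true 13-point reduction in delirium is recorded as a 2.3-point increase.

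These figures model the proportion of patients with any complication. Section 8.2 also analyses the mean number of complications, which they do not cover.

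**The case against.** A reader might infer that sections 3.2 and 5.1 define two contradictory events. The text does not force that. Section 3.2 names the tool and the trigger, section 5.1 names the operator, and they can be read together: the research assistant follows patient and record and applies the 4AT when delirium is suspected. Section 5.1 does not say that every patient is tested. This is an unreconciled ambiguity, not a flat contradiction.

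A reader might also infer that the programme does raise detection and does hide its benefit. The documents do not establish that either:

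- The mechanism needs suspicion to come from ward staff or the G-COMAN nurse. If the research assistant alone raises it, equally in both prospective cohorts, most of the imbalance goes.
- Usual care already has a delirium protocol, so detection there is not zero.
- The 48-hour delirium screen appears only in the fidelity definition of section 5.1. The fidelity list in section 3.3 has only the DOS follow-up, which applies once a patient is already delirious.
- Unblinded assessors may expect the programme to work, which would bias the other way.
- The detection shares are chosen, and the 13% comes from a cardiology ward and may be relative.

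All of this stands and limits the strength of the claim. What survives is that the endpoint definition itself states a suspicion trigger, does not say whose suspicion counts, and is used in an unblinded comparison where only one cohort receives measures that can affect suspicion. That is a rule stated badly in the protocol, not detail merely left for an analysis plan.

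**Conclusion.** The point holds as a possible bias that the protocol leaves open. Sections 3.2 and 5.1 must be reconciled on who is given the 4AT, by whom and when. If ward or programme staff can supply the suspicion, detection may rise in the post-cohort only and may dilute or hide a true reduction in the primary endpoint, including between the two prospective cohorts. The net direction cannot be determined from the documents.

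On the assumptions shown, the any-complication difference falls by about 3 points for small detection gaps and by about 7-9 points for large ones, and power falls from 0.73-0.82 to as low as 0.35-0.37. Part of each fall reflects incomplete detection common to both cohorts. The figures illustrate sensitivity and are not estimates. Other inputs give other values: with true delirium of 40% v 25%, other complications of 33.3% v 20%, and 50%/90% detection, power at 102 per group is 0.24.

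**What to change.** 1. In sections 3.2 and 5.1, state the trigger, the assessor and the schedule of the 4AT actually used in the prospective pre-cohort, and apply the same rule in the post-cohort. A research-assistant 4AT regardless of suspicion should be used only if the pre-cohort was assessed that way. Section 4.3 places pre-cohort inclusion between October 2021 and March 2022, and the synopsis dates this version 22-04-2022. A new universal rule could therefore reach only the post-cohort and would widen the detection gap.
2. Count delirium screens triggered by the programme for fidelity only, not as endpoint events.
3. Pre-specify the primary comparison repeated without delirium, with delirium reported separately, as the sensitivity analysis for interpreting a null or adverse result. This also covers the retrospective pre-cohort, whose complications come from the record only.

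The cost is some wording and one extra analysis. That analysis has fewer events and less power. Under the assumptions above the difference without delirium would be 40 − 28 = 12.0 points (A) or 38.5 − 23.1 = 15.4 points (B), with power of about 0.44 and 0.67 by the same formula. It therefore helps to interpret the primary result but cannot replace it.

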### 3.3 Secondary endpoints

1) Effectiveness evaluation

The secondary endpoints include comparison between the two groups on **patient outcome**:

- Length of hospital stay

- quality of life: EQ-5D^10^ (at admission, discharge, 1 month, 3 months, 6 months and 12 months post-surgery)

- functional status: Parker Mobility Score^11^, modified Barthel Index^12^, Lawton and Brody Scale^13^, Katz index (admission, discharge, 1 months, 3 months and 6 months post-surgery).

- hospital readmissions (30 and 90 days after discharge)

- falls (= “an unexpected event in which the patients comes to rest on the ground, floor or lower level”) and new fractures, either by retrospectively checking electronic patient record for any contact after discharge to any hospital or emergency department stating the occurrence of falls or new fractures) and by a questionnaire send out to patient and care givers. (admission, in-hospital, at discharge, at 1, 3, 6 months post-surgery 12 months post-surgery)

- Living situation: defined in 5 categories: living alone at home, living with spouse/partner, living with children, assisted living, living in a facility with 24h care such as nursing home). Details of care provided will be recorded as one of the following categories: 24h care, daily, irregular, no care. (admission, discharge, 1 month, 3 months post-surgery, 12 months after surgery)

- mortality (in-hospital, 1 month post-discharge and 12 months after discharge)

- secondary fracture prevention: documentation of fall risk assessment, medication review of calcium/vitamin D use and osteoporosis treatment, appointment to fracture liaison service (12 months after surgery)

- nutritional status: Mini Nutritional Assessment (MNA) ^14^ (at admission, 1 month, 3 months and 6 months post-surgery)

- cost-benefit analysis:

Costs will be assessed using a model that registers key hospital activities from the electronic patient record (KWS): 'beeldvorming', 'daghospitalisatie', 'dialyse', 'functiemeting', 'hospitalisatie', 'hospitalisatie ITE', 'labo', 'operatiekwartier', 'paramedische staf', 'raadpleging', 'raadpleging functiemeting', 'radiotherapie', 'spoedgevallen'. The model was developed by UHL.

2. Feasibility evaluation (is the intervention successfully implemented?):

2.1:

- the reach of the program (% of all eligible patients that were included in the G-COMAN program, defined as the patients who completed the questionnaire)

- the fidelity towards the core components of the program (% of included patients who received the core components of the intervention). The core components are 1) the screening questionnaire, 2) comprehensive geriatric evaluation, 3) individual care plan and 4) follow-up.

- The fidelity towards the other intervention components:

- Patient received physiotherapy within 24h postoperative
- The patient was evaluated using the food quadrant method by a logistics employee
- Patient received swallowing screening by a nurse
- If there is no indication for an indwelling catheter, the patient is free of an indwelling catheter
- If a post-void residual volume of ≥ 300 ml is observed in a patient, the residual volume is removed using intermittent catheterization before end of shift after detection of symptoms
- If the urinary catheter was removed, the post-void residual volume is monitored using a bladder scan in the next shift
- If a patient has not passed stool for 3 days, the patient is prescribed oral laxatives before day 4 without stool
- If a patient has not passed stool for 5 days, the patient receives an enema before day 6 without stool
- If there is no indication for a physical restraint, the patients is free of a physical restraint
- If a patient is delirious, the DOS scale was followed up during the next shift
- If a patient reports a pain score of 4 or higher (out of 10), pain medication is given unless refused by the patient within 1h of onset of symptoms
- If a patient reports a pain score of 4 or higher (out of 10), the pain is re-evaluated within 1h of onset of symptoms
- If a patient did not take calcium/vitamin D supplements or anti-osteoporotic medication at admission, it was prescribed at discharge
- The patient was referred to a fracture liaison service

2.2: Implementation targets: awareness, knowledge, motivation to change, perceived acceptability and feasibility, and believe in the benefit, value and success of the program

2.3: Implementation determinants: facilitators and barriers of the program

3. Process evaluation (how well was the process of care changed?)

3.1: reach and fidelity will be reevaluated the same way as expressed above.

3.2: process outcomes

- time to start physiotherapy (as first day after surgery with a first registered contact in electronic patient record)

- % of patients receiving dietary advice and time to start dietary advice

- use and duration of physical restraints (as registered in the electronic patient record; 3-points fixation or higher degrees of fixation)

- use and duration of indwelling catheters (urinary tract catheter or intravenous catheter as registered in the electronic patient record)

- Medication reconciliation at admission and discharge (calcium/vitamin D supplements and AOM)

- referral to geriatric day clinic (appointment to E459 in the year following first admission)

- Referral to fracture liaison services (Zoledronate infusion and/or metabolic bone consultation)

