| Quality of life | EQ-5D | Mobility, self-care, daily activities, pain, anxiety |  | Questionnaire | X | X | X | X | X | X | No |
| Medication | N/A | Use of calcium/Vitamin D supplements and/or  anti-osteoporotic medication  Polypharmacy (≥ 5 medications) |  | Questionnaire  record | X | X | X | X | X | X | Only baseline and discharge via record |
| Falls and fractures history | N/A | Fall = “an unexpected event in which the patient comes to rest on the ground, floor or lower level” |  | Questionnaire  Record | X | X | X | X | X | X | Only baseline and discharge via record |

M = month, FU = follow-up.

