***Process outcomes in the prospective pre- and post-cohort and retrospective pre-cohort.***

| **Variable** | **Instrument** | **Description** | **Score** | **Type of assessment** | **Prospective pre-cohort/post-cohort** | | | | | | **Retrospective pre-cohort** |
| --- | --- | --- | --- | --- | --- | --- | --- | --- | --- | --- | --- |
|  |  |  |  |  | **Admission** | **Discharge** | **1M FU** | **3M FU** | **6M FU** | **12M FU** | **Yes/No** |
| Reach | NA | Only post-cohort: Number of eligible patients included within G-COMAN | NA | NA |  | X |  |  |  |  | Yes |
| Fidelity | NA | Only post-cohort: Number of patients receiving the core components of G-COMAN | NA | NA |  | X |  |  |  |  | Yes |
| Physical therapy | NA | Number of patients receiving physiotherapy  Numbers of days until start physiotherapy | NA | NA |  | X |  |  |  |  | Yes |
| Dietary advice | NA | Number of patients receiving dietary advice  Number of days until start of dietary advice | NA | NA |  | X |  |  |  |  | Yes |
| Physical restraints | NA | Number of patients being restrained  Duration of the use of restraints  Type of restraints used | NA | NA |  | X |  |  |  |  | Yes |
| Indwelling catheters | NA | Number of patients with an indwelling catheter (urinary tract catheter or intravenous catheter)  Duration of catheterization  Reason for catheterization | NA | NA |  | X |  |  |  |  | Yes |
| Medication reconcilliation | NA | Number of patients with calcium/vitamin D supplements and/or AOM | NA | NA |  | X |  |  |  |  | Yes |
| Referral to geriatric outpatient clinic at discharge | NA | Number of patients referred to the falls clinic, memory clinic, follow up | NA | NA |  | X |  |  |  |  | Yes |
| Referral to FLS | NA | Number of patients referred for Zoledronate infusion or metabolic bone consultation | NA | NA |  | X |  |  |  |  | Yes |

M = months, FU = follow-up.

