### 6 months after discharge

Patients or their care givers will receive a letter by post with instructions and an assessment questionnaire for follow-up assessment at 1 month post discharge. In case of no response, the researchers will contact the patient / care giver by telephone to complete the assessment. The following items will be evaluated: **functional status** (Parker Mobility Score, Barthel Index, Lawton and Brody Scale, Katz index), **Quality of Life** (EQ-5D), **nutritional status**, and the **presence of new falls and fractures** as well as the use of calcium/vitamin D and anti-osteoporosis **medication in a questionnaire**. None of the variables can be retrospectively collected.

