### 12 months after admission

**Mortality** will be checked in the electronic patient record (KWS) which is linked the Federale Kruispuntbank and survival status will be double checked with patients/ care givers via questionnaire. **Quality of life** (EQ-5D) and **residential status** will also be checked in the questionnaire. Also the **presence of new falls and fractures** will be asked as well as use of calcium/vitamin D and anti-osteoporosis **medication** in a questionnaire. Only mortality will be retrospectively collected.

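### Falls and new fractures are compared between cohorts up to 12 months, but none are collected after discharge for the retrospective controls

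*Protocol*

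**What the plan says.** Section 3.3 introduces the effectiveness endpoints with "The secondary endpoints include comparison between the two groups on" patient outcome, and falls and new fractures are one of them. The record is one named source, worded (up to the final word, fractures) as "either by retrospectively checking electronic patient record for any contact after discharge to any hospital or emergency department stating the occurrence of falls or new". A questionnaire to patients and caregivers is the other. The time points are "admission, in-hospital, at discharge, at 1, 3, 6 months post-surgery 12 months post-surgery". One definition and one list of time points are given, with no distinction between cohorts.

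Section 3.4 says the pre-cohort will not reach its planned size prospectively and will be topped up with patients whose data are gathered retrospectively. It does not say how many.

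In the flowchart (3.6), the falls and fractures row lists both questionnaire and record as assessment types. It marks all six time points for prospective patients. For the retrospective pre-cohort the entry is "Only baseline and discharge via record".

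Section 5.1 agrees with the flowchart. At discharge, fall history is among the items available retrospectively: "Variables that can be retrospectively collected are as follows: discharge date, medication, mortality, fall history and living situation". At 1 month only mortality and readmission are taken retrospectively, and at 3 months only readmission. At 6 months, "None of the variables can be retrospectively collected". At 12 months, "Only mortality will be retrospectively collected".

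**The concern.** Section 3.3 describes a retrospective record search for post-discharge falls and fractures. Sections 3.6 and 5.1 do not apply that search to the patients who can be followed only through the record. As scheduled, the post-cohort and the prospective controls are to be followed for this endpoint to 12 months, while the retrospective controls are followed to discharge.

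The shortfall is built into one arm. Either the post-discharge comparison silently shrinks to the prospective controls, or the two arms are observed over different periods and by different sources. The protocol does not say which controls enter the comparison. This goes beyond what an analysis plan can settle, because the schedule determines whether the data exist at all.

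**Working it through.** **1. Retrospective controls: the endpoint definition against the schedule**

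| Time point | Section 3.3 (both groups) | Sections 3.6 and 5.1, retrospective controls |
|---|---|---|
| Baseline | falls and fractures | taken from the record |
| Discharge | falls and fractures | taken from the record |
| 1 month | falls and fractures | mortality and readmission only |
| 3 months | falls and fractures | readmission only |
| 6 months | falls and fractures | nothing |
| 12 months | falls and fractures | mortality only |

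The two columns agree up to discharge and disagree at each of the four later time points.

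**2. Is the record already used for these patients after discharge?** Yes. Readmission at 1 and 3 months and mortality at 12 months are collected for them retrospectively (3.6 and 5.1). The 12-month mortality check is a survival-status lookup through a linked registry, not a review of hospital contacts, so the added work is real.

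**3. Size of the loss.** The protocol gives no event rate, power or precision target for falls or fractures, so there is no stated figure to reproduce for this endpoint. The 108 per group in section 8.1 was derived for in-hospital complications and is used here only as the group size.

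Inputs:
- Post-cohort: 108 (section 8.1).
- Controls planned: 108 (section 8.1).
- Retrospective share *s*: not stated, so assumed at 30%, 50% and 60%.

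Controls with post-discharge data: n_c = 108 × (1 − s).

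With a similar outcome variance in both groups, the standard error of the difference, relative to full data, is

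ratio = √[(1/108 + 1/n_c) / (2/108)] = √[(1 + 108/n_c) / 2].

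| Assumed s | n_c | Calculation | Ratio | Rise in standard error |
|---|---|---|---|---|
| 30% | 75.6 | √[(1 + 1.429)/2] = √1.214 | 1.10 | about 10% |
| 50% | 54 | √[(1 + 2)/2] = √1.5 | 1.22 | about 22% |
| 60% | 43.2 | √[(1 + 2.5)/2] = √1.75 | 1.32 | about 32% |

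These figures isolate the effect of the schedule. Death, loss to follow-up and unreturned questionnaires would reduce both arms further and are not included.

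**The case against.** The strongest defence is that the restriction is deliberate and disclosed. The flowchart and the visit text agree with each other, and function, nutrition, quality of life and living situation are limited in a similar way for retrospective controls. The follow-up visits in 5.1 describe falls and fractures by questionnaire, and the sentence in 3.3, which runs from an either to an and, does not say which cohort the record search covers. Comparing post-discharge falls in prospective controls only would also be a coherent design.

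Much of this stands. The wording of 3.3 is ambiguous, and the restriction may be intended. But falls and fractures differ from those other outcomes, because 3.3 itself names the record as a source for them after discharge. Nor does the protocol say that the comparison is confined to prospective controls.

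A reader might infer more than the document supports:
- **That these controls have no data on this endpoint.** They have baseline and discharge data; only 1 to 12 months is missing.
- **That they will be counted as event-free, making the programme look harmful.** No rule in the protocol says so.
- **That the post-cohort will be complete.** Follow-up is scheduled for all of them, but it relies largely on posted questionnaires with telephone back-up, and section 8 anticipates losses.
- **That fracture liaison referral has the same control-arm gap.** It does not. The process-outcome table in 3.6 ("Number of patients referred for Zoledronate infusion or metabolic bone consultation") is marked as available for retrospective controls, at the same discharge time point as for the other cohorts. Section 3.3 dates the fracture liaison appointment at 12 months after surgery instead, which is a separate inconsistency affecting both cohorts alike.

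**Conclusion.** The point holds for post-discharge falls and new fractures, 1 to 12 months, in the retrospective part of the pre-cohort. Section 3.3 cannot be carried out as written under the schedule in 3.6 and 5.1, and the resulting loss is confined to the control arm. For assumed retrospective shares of 30% to 60% of 108 controls, the standard error of the between-group difference rises by about 10% to 32%. The true figure depends on a share the protocol does not give.

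The consequence is lost precision, or unlike ascertainment between arms, for one secondary endpoint. The primary endpoint is unaffected. The document does not support predicting a bias in a particular direction. The change is worth making because, without it, the missing outcomes cannot be recovered at the analysis stage.

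**What to change.** Reconcile 3.3, 3.6 and 5.1 by amendment:

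1. Extract new fractures, and falls leading to a hospital or emergency contact, from the electronic record to one fixed 12-month point in all patients: retrospective pre-cohort, prospective pre-cohort and post-cohort. State the origin of the 12 months, since 3.3 counts from surgery and the 12-month visit in 5.1 counts from admission.
2. Use this common-source version for the comparison that includes retrospective controls.
3. Report questionnaire falls separately, for prospective controls against the post-cohort.

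If the sponsor prefers not to extend the extraction, the minimum is to state that post-discharge falls and fractures are compared using prospective controls only, and to accept the loss of precision.

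The cost is amendment wording and some extra record extraction. The record misses falls without a hospital contact and may miss contacts elsewhere. Under-recording cannot be assumed equal in the two cohorts: follow-up is a core component of the programme and could raise documentation of falls in the post-cohort. Fractures are therefore the more robust component and should be shown separately from falls.
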